## Abstract

**Background:**

In cardiac surgical procedures, patients carrying high-risk profiles are prone to encompass complicated cardiopulmonary bypass (CPB) separation. Intraoperative transesophageal echocardiography (TEE), a readily available tool, is utilized to detect cardiac structural and functional pathologies as well as to facilitate clinical management of CPB separation, especially in the episodes of hemodynamic compromise. However, the conventional TEE examination, always performed in a liberal fashion without any restriction of view acquisition, is relatively time-consuming; there appear its flaws in the context of critically severe status. We therefore developed the perioperative rescue transesophageal echocardiography (PReTEE), a simplified three-view TEE protocol consisting of midesophageal four chamber, midesophageal left ventricular long axis, and transgastric short axis.

**Methods:**

This is a single-center and randomized controlled trial which will be implemented in Peking Union Medical College Hospital, Beijing, China. A total of 46 TEE scans are schemed to be performed by 6 operators participating in and randomly assigned to either the PReTEE or the conventional TEE group. This study is purposed to investigate whether the efficiency of discriminating leading causes of difficult CPB wean-off can be significantly improved via an abbreviated sequence of TEE views. The primary outcome of interest is the difference between the groups of PReTEE and the conventional TEE in the successful discrimination of etiologies in specified 120 s. Cox proportional hazards model will be further employed to calculate the outcome difference.

**Discussion:**

The estimated results of this trial are oriented at verifying whether a simplified TEE exam sequence can improve the efficiency of etiologies discrimination during CPB separation in cardiac surgery.

**Trial registration:**

ClinicalTrials.gov NCT05960552. Registered on 6 July 2023.

**Supplementary Information:**

The online version contains supplementary material available at 10.1186/s13063-024-08338-9.

### Introduction

#### *Background and rationale* {6a}

Patients undergoing cardiac surgical procedures usually encounter a complexity of cardiopulmonary bypass (CPB) separation due primarily to hemodynamic compromise [1, 2]. The explainable determinants linked with difficult separation are multiple; increased age, critical comorbidities, redo cardiac surgery, poor cardiac function, a history of myocardial infarction, and complicated cardiac etiologies can all enhance the risk of its unexpectable onset [1]. When a difficult CPB separation is anticipated, not only more assisted inotropes and mechanical cardiac support are required [3–5] but also the clinical adverse consequences have been evidenced to be somewhat detrimental, such as high perils of morbidity and mortality [1]. Notably, there exists no standard protocol or guideline with regard to management of difficult CPB wean-off yet. The cause discrimination and rapid decision-making adoptions should therefore be equally emphasized in separation process.

Transesophageal echocardiography (TEE) utilized in the cardiac surgical scenario has been recognized as a predominant and reliable tool in revealing potential causes of failure to wean from CPB [2]. It can timely and efficiently provide vital clues, combined with compromised hemodynamic parameters, in identifying underlying reasons [2, 6, 7]. The vital role of intraoperative TEE has been fiercely unfolded out in surgical decision-making [8], peri-operative management [2], and clinical outcome improvements [9, 10].

Nevertheless, the conventional TEE scan sequence is time-consuming due to examinations without any restrictions of views, especially the rescue time the cardiac anesthesiologists and surgeons confronted with is relatively pushed. We initiate the program of perioperative rescue transesophageal echocardiography (PReTEE), attempting to simplify scan sequence and to focus collectively on a combination of three valuable views of midesophageal four chamber (ME 4C), midesophageal left ventricular long axis (ME LV LAX), and transgastric short axis (TG SAX). This simplified three-view TEE sequence derived objectively from clinical experience, in comparison with traditional TEE via a comprehensive or liberal examination, aims at detecting out the cardiac etiologies in a more prompt and accurate fashion.

### *Objectives* {7}

The primary objective is to assess whether PReTEE protocol can facilitate the TEE operators swiftly undertake an evaluation, as well as accurately discriminate the leading causes and accompanied cardiac pathologies in the phase of CPB separation, thereby yielding significant improvement regarding diagnostic efficiency.

### *Trial design* {8}

This is a single-center and randomized controlled trial which will be prospectively conducted at Peking Union Medical College Hospital, Beijing, China. The six TEE operators participating in this trial will be randomly assigned in a 1:1 fashion into the PReTEE group and the conventional TEE group. This protocol strictly conforms to the Standard Protocol Items Recommendation for Interventional Trials (SPIRIT) Checklist (Table 1).

**Table 1 Tab1:** SPIRIT flow diagram. *PReTEE* perioperative rescue transesophageal echocardiography, *TEE* transesophageal echocardiography

	**Enrolment**	**Allocation**	**Post-allocation**	
Timepoint**	**Pre-allocation** **-t**_**1**_	**Preoperative** **0**	**Procedure** **t**_**1**_	***t***_***2***_
Enrolment:				
Eligibility screen	X			
Informed consent	X			
Allocation		X		
Interventions:				
PReTEE			X	X
Conventional TEE			X	X
Assessments:				
Outcome measurements			X	X
Adverse event evaluation			X	X

## Methods: participants, interventions and outcomes

### *Study setting* {9}

Our trial will be implemented from August 1, 2023, to August 1, 2025, at the Peking Union Medical College Hospital, a tertiary hospital in Beijing, China. Patient selection will be initiated following reviewing electronic system the day before surgery, based primarily on the inclusion and exclusion criteria. Then in cardiac wards, a detailed introduction of this trial as well as salutary and harmful effects should be reached out to the candidate patients in a popular and understood way. The informed consents must be signed if patients decide to participate in this trial owning to their willingness. The investigators in charge of patient recruitment should solve puzzles regarding this trial raised by patients.

### *Eligibility criteria* {10}

A patient who fulfills all of the following criteria will be included:

Male or female patients aged ≥ 18 years.Patients who will undergo elective cardiac surgery with CPB.Patients with high-risk profile as one of the followings: left ventricular ejection fraction of 50% and fewer, coronary artery bypass graft concomitant with valve procedures, multiple valve procedures, Euroscore > 6 or re-do cardiac surgery.Patients who sign the informed consent to participate in the study.

The exclusion criteria are listed as follows, and a patient who meets any of the criteria will not be considered.

Gastrointestinal surgery history.Active upper gastrointestinal bleeding.Esophageal abnormality: stricture, tumor, fistula/ulcer, diverticulum, or recent perforation.Non-elective cardiac procedures.The requirement for mechanical cardiac support (extracorporeal membrane oxygenation, intra-aortic balloon pump, left ventricular assisted device) prior to cardiac surgery.

### *Who will take informed consent* {26a}

Patients who fulfill the inclusion and exclusion criteria after assessment will be invited to participate in this clinical trial in cardiac wards the day before cardiac surgery. The chief investigator will present detailed descriptions of purpose, trial protocol, and likelihood harms and benefits. Any query raised by eligible candidates must be solved as well. Informed consent, given in writing, must be given owning to patient willingness, and any withdrawal from this study at any time at patient’s own request must be allowed. A unique number will be assigned to patients who are ultimately enrolled into our program. Additionally, TEE operators participating in this trial are required to sign the informed consent.

### Additional consent provisions for collection and use of participant data and biological specimens {26b}

N/A, because no biological specimens or data associated will be collected in this trial.

## Interventions

### Explanation for the choice of comparators {6b}

Six TEE operators, willing to participate in this trial, are all junior cardiac anesthesiologist fellows at our institute whose accumulation of TEE performances are relatively comparable. They will be randomly assigned into the TEE groups stratified by allocation prior to trial initiation, with three in each group. The three operators in the PReTEE group will be required to accomplish the TEE examinations using a simple sequence of ME 4C, ME AV LAX, and TG SAX. On the other hand, another three in the conventional cohort will perform TEE examinations in a liberal fashion, that is, without any restriction on scan sequence.

### Intervention description {11a}

General cardiac anesthesia induction and maintenance will be prescribed at the chief anesthesiologist’s discretion. CPB procedure at our institute complies with a standardized pattern. The separation of CPB is ended with the administration of protamine and the removal of the venous and arterial cannulas. All patients during intraoperative periods will receive a round of TEE examination before and after CPB routinely. Hemodynamic parameters and TEE findings are two major determinants in the process of CPB separation. Following the completion of surgical procedures, patients will be admitted to the intensive care unit for further advanced monitoring and therapy. The timing of transfer from intensive care unit to the general ward will depend on patient physical recovery status.

When the process of CPB separation initiated, the TEE probe is immediately inserted by the TEE operators. Then they are required to remove and rotate the probe and to promptly detect the leading causes of complex CPB separation. After the probe is well inserted, the time taken in seconds till TEE scan completion will be measured by the study recorder. The etiology interpretations and their corresponding TEE views will also be reported to the recorder by operators and simultaneously kept in a form of questionnaire (Supplemental file 1). The maximum time for TEE sequence scanning permitted is 120 s. The number of both junior TEE operators and eligible patients available at our institute are to some extent of limitation; therefore, TEE examination for each patient is not conducted by equal numbers of operators stratified by allocation groups. During patient examinations by operators and the expert, the TEE probe is kept still.

The successful diagnosis is defined as the correct cause of discrimination within the specified 120 s. If an operator does not report any diagnoses or reports the uncorrected ones, a failure will be assigned. All TEE examinations in both groups will be supervised by the expert, who guarantees the safety of this study but does not facilitate the image obtainment or interpretation. The TEE results within this trial will also be finalized by the expert. TEE operators who finish the sequence scan and diagnosis report will immediately leave the operating room, therefore precluded from observing the expert’s TEE examination. The TEE expert finally will rate the cause discrimination per examination by the operators with a 5-point scale system (1 point, absolutely wrong; 2 points, wrong; 3 points, average; 4 points, correct; and 5 points, absolutely correct) (Supplemental file 1). There is no application of scoring system on the clarity of TEE view acquisition, as the TEE operators participating in this trial have obtained TEE manual skills. During the study period, the TEE machine we employ is Philips Ultrasound iE33 and the probe is Philips Ultrasound X7-2t.

Following the completion of TEE operators’ assessment, the TEE expert will routinely perform a standard comprehensive TEE examination. The cause provided by the TEE expert will be directly communicated to the attending anesthesiologist and cardiac surgeons, independent from this study, referred as therapeutic approach.

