### Sample size {14}

In our preliminary experiment, the time of finding out the cardiac etiologies in the PReTEE group was 36 s, whereas in the conventional group was 100 s. The preliminary results have never been published. Twenty PReTEE exams were performed using the available simulator employed at our center. Considering the apparent reduction of timing of diagnosis, no further PReTEE exams are planned to be conducted in cardiac surgical patients. However, one TEE scanning procedure in the conventional group was implemented for one cardiac patient in the operating room. To achieve a 90% power at a significance level of 5%, 42 TEE examinations should be conducted among eligible patients using a hazard ratio of 2.78. Considering a 20% dropout rate, a total of 46 TEEs are schemed to be consecutively performed. The sample size calculation was achieved using the gsDesign package via R software.

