## Statistical methods

### Statistical methods for primary and secondary outcomes {20a}

The R software will be ultimately employed to perform all statistical analysis. The continuous data will be summarized as median (standard deviation) or median (interquartile range), whereas categorical data as number (percentage). Based on the time to event in the process of estimating the difference regarding diagnostic efficiency between the conventional TEE group and the PRe TEE group, a Cox proportional hazards model will be considered. In the Cox model, we will treat the TEE operators who failed the diagnosis as censored. A *P* < 0.05 will be considered statistically significant.

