### Methods in analysis to handle protocol non-adherence and any statistical methods to handle missing data {20c}

The loss regarding the times of TEE scan by operators in each cardiac surgical procedure will be controlled by adhering to the trial methods depicted above. We suppose that the number of missing data would be relatively limited. The dropout rate of 20% is also accounted for when calculating the sample size.

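### Scans can share a patient, possibly across arms, but the sample size and the Cox model treat them as independent; the direction of the resulting error depends on a scanning pattern the protocol does not state

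*Protocol article*

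**What the plan says.** All references are to the protocol article.

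- **Randomisation.** Trial design {8}: "The six TEE operators participating in this trial will be randomly assigned in a 1:1 fashion". The comparator section {6b} adds "with three in each group". Neither patients nor scans are randomised.
- **Scans per patient.** Intervention description {11a}: "TEE examination for each patient is not conducted by equal numbers of operators stratified by allocation groups". The missing-data section {20c} speaks of "The loss regarding the times of TEE scan by operators in each cardiac surgical procedure", again with more than one operator per procedure. In {11a} the expert examines the patient after the operators have finished, and under Outcomes {12} an operator's diagnosis is correct or not by agreement with the expert. Scans of one patient therefore share the pathology, the imaging conditions and the reference diagnosis.
- **Sample size {14}.** "To achieve a 90% power at a significance level of 5%, 42 TEE examinations should be conducted", "using a hazard ratio of 2.78". Then: "Considering a 20% dropout rate, a total of 46 TEEs are schemed to be consecutively performed".
- **Primary analysis {20a}.** For the comparison of the two groups, "a Cox proportional hazards model will be considered", with failed diagnoses censored. Neither a patient nor an operator term is named.

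**The concern.** An easy or difficult patient speeds up or slows down every scan of that patient. If those scans come from both arms, the shared variation cancels from the arm contrast. A plain Cox test still counts it as noise, and leaving the patient effect out also pulls the hazard ratio towards 1. If those scans all come from one arm, the shared variation adds to the arm contrast and the plain test understates its variance. In either case the p value and confidence interval do not match the design.

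A second dependence runs alongside. Each operator belongs wholly to one arm and performs many scans, so differences between operators are confounded with the arm contrast. This is a different structure from patient sharing, and handling one does not remove the other.

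**Working it through.** **1. The plan's own figure.** Inputs from {14}: hazard ratio 2.78 (= 100 s / 36 s), 90% power, 5% level (two-sided assumed, as sidedness is not stated), 1:1. Schoenfeld: events = 4(1.960 + 1.282)² / (ln 2.78)² = 42.0 / 1.045 = 40.2, so 41, or 42 in equal arms. The stated 42 is reproduced. The formula assumes independent scans, each ending in an event, and makes no allowance for shared patients or operators.

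**2. Direction of the error.** The protocol gives no correlation, so the values here are assumptions. Let ρp and ρo be the patient and operator intraclass correlations, k the scans per patient, d the difference between arms in scans of that patient, and 46/6 = 7.67 the scans per operator. The true variance of the difference in arm means, relative to the variance under independence, is approximately

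R = 1 + ρp(d²/k − 1) + ρo(7.67 − 1),

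and the actual two-sided error of a nominal 5% test is 2[1 − Φ(1.96/√R)].

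With ρp = 0.3 and ρo = 0 (46 does not divide evenly in every pattern, so values are rounded):

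| Scans per patient (arm : arm) | R | Type I error |
|---|---|---|
| 1:1 | 0.70 | 0.019 |
| 2:1 / 1:2 | 0.80 | 0.029 |
| 3:1 / 1:3 | 1.01 | 0.051 |
| 2:0 / 0:2 | 1.30 | 0.086 |
| 3:0 / 0:3 | 1.59 | 0.120 |

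The same omission makes the test conservative, about right or anti-conservative, according to the pattern.

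**3. Power.** Simulation settings, all assumed beyond {14} and {11a}: 46 scans, exponential times with conventional median 100 s, hazard ratio 2.78 given the patient, censoring at 120 s, lognormal patient effect, no operator effect. The plain log-rank (Cox score) test is compared with an exponential gamma shared-frailty model. Patient SDs of 0.5, 0.74 and 1.0 correspond to correlations on log time, SD²/(SD² + π²/6), of 0.13, 0.25 and 0.38. Power in %, plain/frailty, 500 trials per cell:

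| Pattern | SD 0.5 | SD 0.74 | SD 1.0 |
|---|---|---|---|
| 1:1 | 78/83 | 67/80 | 58/77 |
| 2:1 / 1:2 | 77/81 | 73/82 | 53/74 |
| 3:1 / 1:3 | 71/75 | 66/74 | 57/72 |
| mixed 3:2, 2:1, 1:1 | 76/81 | 68/80 | 53/77 |

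The mean gaps are (5+4+4+5)/4 = 4.5, (13+9+8+12)/4 = 10.5 and (19+21+15+24)/4 = 19.8 points. A separate run gave about 5, 10 to 12 and 16 to 21. Plain type I error was about 2 to 6% when both arms scan the same patients and 8 to 9% when each patient is scanned by one arm. In that last pattern the frailty lowered nominal power (61.3% to 54.0% in one run).

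**4. Operators.** With one scan per patient, R = 1 + 6.67ρo. At ρo = 0.05, 0.1 and 0.2 this is 1.33, 1.67 and 2.33, and type I error is 0.090, 0.129 and 0.20. Even with 1:1 sharing at ρp = 0.3, the same ρo values give 0.054, 0.094 and 0.169. In simulation with an operator log-hazard SD of 0.3, a patient frailty without an operator term had type I error of about 7 to 13% when both arms scan the same patients. At patient SD 0.74, operator SD 0.5 and 1:1, it was 14.5% against 8.5% for the plain test.

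**5. Stratifying instead of a frailty.** With 1:1 pairs and no operator effect, strict stratification by patient moved power from 0.76 to 0.62 (patient SD 0.5) and from 0.56 to 0.62 (SD 1.0), so it is not a reliable substitute.

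**The case against.** **The model detail may be in an analysis plan that is not shown.** A condensed article often omits frailty or cluster terms, and the wording in {20a} does not exclude them. This carries weight: if such a plan names both terms, the point shrinks to the sample size. But the article itself sets up the shared-patient structure, and its 42 comes from a formula for independent scans. Followed as written, the two do not fit.

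**A reader might infer that scans are paired within patients, so that the test is too conservative and much power is lost.** The document does not support this. It says the numbers of operators from the two groups are unequal, fixes no pattern, and does not say that every patient is scanned by both arms. Conservatism needs near-balanced arms within patients and little operator variation. The larger power gaps need a large patient SD and no operator effect, and they favour the frailty somewhat because its baseline matched the simulated one. A simple large-sample calculation with 42 events and 1:1 pairs, without the 120 s cap or the dilution of the hazard ratio, gives a loss of only 1 to 3 points (92% against 94% at ρp = 0.1; 95% against 98% at 0.3).

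**A reader might also infer that a patient term is enough.** Step 4 of the working shows otherwise.

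**Complications.** The document lists their incidence but states no comparison between arms, so nothing there is wrong as written. The point is only that a patient scanned by both arms and then by the expert has one injury outcome, which cannot be attributed to an arm.

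**Conclusion.** The point holds in conditional form. The protocol lets scans share a patient and a reference diagnosis, sizes the trial as if scans were independent, and names a primary model without a patient term. The direction and size of the error cannot be fixed from the document, because it gives neither the scanning pattern nor any correlation.

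Under the assumed SDs and no operator effect, power is lost where both arms scan the same patients, by the amounts in step 3, and false positives rise where each patient is scanned by one arm only. Once moderate operator variation is allowed, inflated type I error is the main risk, and it is probably larger than the effect of patient sharing. The combined patient-and-operator model was not itself simulated, so the power gaps are not a promise of what the fix below will deliver.

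**What to change.** In {20a}, specify the primary Cox model with crossed random effects for patient (as a shared frailty, not strict stratification) and operator, and base inference on the arm effect on a method that respects six operators. Use the same two terms for the per-scan detection-rate endpoints. In {11a}, state how operators of each arm are assigned to a patient. Report TEE complications once per patient for the whole cohort, without attributing them to an arm in patients scanned by both.

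The cost is mainly wording. Each patient already receives a unique number (consent section {26a}), and the operator of each scan needs to be kept with the scan record. The downsides are variance parameters that 46 scans will estimate imprecisely, a possible small loss of nominal power if each patient turns out to be scanned by one arm, and no arm-wise complication rate in shared patients.

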### Outcomes {12}

#### Primary endpoint

The primary endpoint we define is the difference in terms of correctly discriminating causes in the phase of CPB separation within specified 120 s between the PReTEE group and the conventional TEE group. A correct diagnosis by TEE is defined as the extent of agreement up to 70% and greater between the conventional TEE/PReTEE and the expert TEE; otherwise, an uncorrected diagnosis would be accounted for.

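### The expert who sets the reference diagnosis is not kept from the operators' answers, so agreement with the expert, the primary outcome, can be biased by an amount and in a direction that the plan does not allow one to determine

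*Protocol article*

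**What the plan says.** The relevant statements in the protocol article are these.

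- **Supervision** (Intervention description {11a}): "All TEE examinations in both groups will be supervised by the expert, who guarantees the safety of this study". The same sentence adds that the expert gives no help with obtaining or interpreting images.
- **Operators' report** ({11a}): "The etiology interpretations and their corresponding TEE views will also be reported to the recorder by operators", and it is kept on a questionnaire.
- **Shielding of operators** ({11a}): once they have scanned and reported, operators "will immediately leave the operating room, therefore precluded from observing the expert’s TEE examination".
- **Reference examination** ({11a}): "Following the completion of TEE operators’ assessment, the TEE expert will routinely perform a standard comprehensive TEE examination".
- **Final result and rating** ({11a}): "The TEE results within this trial will also be finalized by the expert", and "The TEE expert finally will rate the cause discrimination per examination by the operators with a 5-point scale system".
- **Primary endpoint** (Outcomes {12}): a diagnosis is correct given "agreement up to 70% and greater between the conventional TEE/PReTEE and the expert TEE".
- **Blinding** (Who will be blinded {17a}): experts are listed as unaware of the allocation groups. Unawareness of the operators' answers is not mentioned.

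**The concern.** One person watches the index examination, then forms the reference standard, and then grades the match between the two. The plan deals with independence explicitly, but in one direction only: operators cannot see the expert's examination, while nothing keeps an operator's stated cause from the expert until the reference is fixed.

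If the expert is drawn towards a cause already named, a wrong report is scored as correct. Some of the findings are open to this, because they rest on visual judgement: under Secondary endpoints, left ventricular systolic dysfunction is assessed by eye. In the Cox model (Statistical methods {20a}) failed diagnoses are censored, so a wrongly credited scan also becomes a false event. The problem would remain even if the expert were perfectly blinded to the arm.

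**Working it through.** The plan states no figure on this point, so there is none to reproduce. The check has two parts.

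**1. Order of events under {11a}**

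1. The operator scans, with the expert supervising.
2. The operator reports the cause to the recorder, then leaves. The report is therefore made before departure, while the expert is supervising.
3. The expert performs the comprehensive examination.
4. The expert finalizes the result and rates each operator's cause.

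Step 4 requires the expert to know the answers. No statement places the recording of the reference before that knowledge, and {17a} covers allocation only. Exposure before step 3 is possible, but it is not stated to occur.

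**2. What such influence would do to the arm difference**

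Every input here is an assumption, except that {11a} counts two kinds of failure: a wrong report and no report. Let p be true success, w the share of wrong reports, and a the share of wrong reports in which the reference moves to the named cause. A non-report names no cause and cannot attract the expert. Hence

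observed success = p + a × w.

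With the same a in both arms, observed difference = true difference + a × (w in PReTEE − w in conventional).

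Assume true success of 85% (PReTEE) and 60% (conventional), a difference of 25 points.

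| Scenario | a = 0.2 | a = 0.3 | a = 0.5 |
|---|---|---|---|
| All failures are wrong reports (w = 15% and 40%): 25 − 25a | 20 points | 17.5 points | 12.5 points |
| Conventional failures are 10% wrong and 30% non-reports (w = 15% and 10%): 25 + 5a | 26 points | 26.5 points | 27.5 points |

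At a = 0.3 the first row is 0.85 + 0.3 × 0.15 = 89.5% against 0.60 + 0.3 × 0.40 = 72%. The second is 89.5% against 0.60 + 0.3 × 0.10 = 63%.

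*Unequal influence, no true difference.* Take p = 60% and w = 40% in both arms, with a = 0.50 in one and 0.25 in the other. Then 0.60 + 0.50 × 0.40 = 80% and 0.60 + 0.25 × 0.40 = 70%. This is a spurious 10 points, favouring whichever arm has the larger a. Unequal influence is conceivable because a supervising expert may be able to tell a fixed three-view sequence from a liberal one.

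*Shared reference.* {11a} says that patients are not examined by equal numbers of operators from each group, which suggests that several operators may scan one patient. If two disagree and the reference moves to the wrong one, that operator gains a success and the other loses a correct one. The formula above does not cover this.

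*Sensitivity to single scans.* If the 42 examinations in Sample size {14} split equally, each arm has 21. One re-scored scan then moves that arm's success by 1/21 = 4.8 points.

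**The case against.** The strongest reply is that exposure is inferred. Answers go to the recorder on a questionnaire that is not shown. The document does not say they are spoken aloud, and the rating is described as coming last, which is compatible with a reference already set. An article may leave such working detail to the full protocol. The expert also performs a fuller examination whose result goes straight to the treating team, which is good reason not to defer to a junior fellow.

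Much of this stands. Exposure is possible rather than stated, and large values of a are hard to credit. It does not remove the point. The article does not leave independence to another document: it sets out who is shielded from what, and the shielding runs one way. The bar on helping operators stops the expert influencing them, not the reverse.

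A reader might infer more: that agreement is in fact inflated in both arms and that the arm difference therefore shrinks. The documents do not support that. Inflation needs exposure and deference, and neither is stated. Shrinkage holds only if the conventional arm has more wrong reports and influence is equal. With a 120 s limit and preliminary times of 36 s and 100 s in Sample size {14} (the latter apparently from a single conventional scan), conventional failures may well be non-reports, and the difference can then widen. Nor does a pull towards one named cause necessarily carry a scan over the 70% threshold.

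**Conclusion.** The point holds as a gap in the design. Followed as written, the plan allows the reference for the primary endpoint to be formed by someone who already knows the answers it will judge, so agreement can be biased. Neither size nor direction can be derived from the document. Equal influence on wrong reports dilutes the difference when the conventional arm has more of them. Non-reports, unequal influence, or several operators sharing one reference can move it either way. The figures under the working are scenarios on assumed values, not estimates. The sponsor should change this; confidence is medium, because exposure is not stated and the questionnaire is not shown.

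**What to change.** In Intervention description {11a}, state that:

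- the operator gives the cause to the recorder in writing and does not speak it to the expert, and the recorder stamps the time at the operator's signal;
- the expert completes and signs a reference form (leading cause, each condition present or absent) straight after the comprehensive examination and before seeing any operator questionnaire;
- the 70% agreement in the primary endpoint is computed from the two locked forms;
- the 5-point rating is kept, but done only after the reference form is locked.

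The cost is one extra form and a few seconds of writing; stamping the time at the signal keeps the writing out of the measured time. No extra staff or examination is needed, and neither the expert's safety supervision nor the communication of findings to the treating team changes. The expert still sees the live scan, so independence is improved but not complete, and the protocol should acknowledge this.
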